### 3. Objectives, Endpoints and Assessments

#### **Primary objective**

*Assess whether 1-2 fractions of 8 Gy is non-inferior to 5 fractions of 5 Gy with respect to target symptom relief.*

Endpoint: Change in the average (last 24 hours) patient-reported target symptom intensity from baseline (BL) assessed after 12 weeks of follow -up

Assessment: Numerical Rating Scale (NRS) score (0-10)

#### **Secondary objective**

*To assess the efficacy of 1-2 fractions of 8 Gy compared to 5 fractions of 5 Gy with respect to:*

- Physician-reported toxicities

Endpoint: Bladder and bowel toxicity after 4, 12 and 52 weeks of follow-up

Assessment: Common Terminology Criteria for Adverse Events (CTCAE) v 5.0

- Survival

Endpoint: Overall survival (OS) assessed at the end of study

#### **Exploratory objectives**

*1. To assess the efficacy of 1-2 fractions of 8 Gy compared to 5 fractions of 5 Gy with respect to:*

- Patient-reported QoL

Endpoint: Change in QoL from BL after 4, 8, 12 and 26 weeks of follow-up

Assessment: European Organization for the Research and Treatment of Cancer Quality of Life Questionnaire-Core15 Palliative (EORTC QLQ-C15 PAL)

- Physician-reported toxicities

Endpoint: All relevant toxicities after 4, 12 and 52 weeks of follow-up

Assessment: CTCAE v 5.0

- Patient reported symptomatic effect

Endpoints: Change in target symptom intensity from baseline after 4 weeks and 26 weeks of follow-up, and changes in intensity of symptoms related to the irradiated tumor other than target symptom (within the five predefined categories) from baseline after 4, 8, 12 and 26 weeks of follow-up

Assessment: NRS score 0-10

- Patient satisfaction

Endpoint: Assessment of patient satisfaction after 4, 8, 12 and 26 weeks of follow-up

Assessment: Patient Global Impression of Change (PGIC)

2. *To explore prognostic models for patient classification*

Endpoint: Correlation between prognostic scores assessed at baseline and overall survival

Assessment: Glasgow Prognostic Score (GPS), LabPS- score and LabBM- score

3. *To explore clinical factors as explanatory response variables*

Endpoint: Correlation between clinical factors and symptomatic response

Assessment: Baseline registration of clinical factors from medical records

4. *Assess hypoxia biomarkers on medical images and biopsies that are previously acquired for diagnosis or treatment, and explore their potential as explanatory response variables in individual patients.*

Endpoint: Correlation between hypoxia biomarkers and symptomatic response

Assessment: Hypoxic fraction assessed by Consumption and Supply-based Hypoxia (CSH)-imaging on MRI (Magnetic Resonance Imaging) and hypoxia-activated protein and gene expression assessed by molecular analyses on tumor biopsies

5. *Assess PD-L1 (Programmed Death-Ligand1)-status in biopsies previously acquired for diagnosis or treatment, and explore potential as explanatory response variable.*

Endpoint: Correlation between PD-L1-status and symptomatic response

Assessment: PD-L1 expression level (all cells) assessed by immunohistochemistry

6. Compare the health-economic aspects in the two study arms regarding

- *Patient-reported QoL*

Endpoint: Change in QoL compared to baseline assessed after 4, 8, 12 and 26 weeks

Assessment: EQ-5D-5L (5 Level-EuroQol-5 Dimensions)

- *Health service costs*

Endpoint: Difference in costs related to attendance at the radiotherapy unit, transportation and hospital submissions

Assessment: Registration of costs from medical records

## 4. Study Design

### 4.1. Overall Design

This is a prospective, randomized, open-label, national, parallel-arm non-inferiority phase III study designed to establish non-inferiority of radiotherapy with 1-2 fractions of 8 Gy to 5 fractions of 5 Gy (active comparator) with respect to patient-reported symptomatic relief. The study population includes patients with gastrointestinal, urological, or gynecological cancer considered as candidates for palliative radiotherapy due to symptomatic pelvic soft tissue tumors. Patients must have an expected survival beyond 12 weeks. Patients will be included over 2-4 years. Eligible patients identified in the screening period will be randomized to either arm A or arm B with an allocation ratio of 1:1 after collection of a signed informed consent. Study-specific baseline evaluation will be performed between date of signed informed consent and intervention start.

Patients in arm A will initially be treated with a single fraction of 8 Gy. In case of unsatisfactory symptom relief after 4 weeks of follow-up, a second radiotherapy fraction may be offered if at least one of the following two predefined criteria are met: 1)  $\leq 2$  point improvement on the NRS-scale and 2) initial symptomatic effect, but rapid deterioration ([Section 4.3.1](#)). Primary and secondary endpoints will be assessed after 4, 8, 12, 26 and 52 weeks of follow-up (last visit, toxicities only) after completed radiotherapy. Subjects will be followed with respect to overall survival until death or censoring (loss to follow-up, study withdrawal, or end of study).

The study timeline is presented in Figure 1.

[figure not shown]

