Abbreviations: AE=Adverse Event, CT= Computed Tomography, CTCAE= Common Terminology Criteria Adverse Events, CRP= C-reactive protein, ECOG = Eastern Cooperative Oncology Group, EORTC QLQ-C15 PAL= European Organization for the Research and Treatment of Cancer Quality of Life Questionnaire-Core15 Palliative, GPS= Glasgow Prognostic Score, LDH=Lactate dehydrogenase, NRS=Numerical Rating Scale, SAE=Serious Adverse Event, WOCBP=Women of childbearing potential

a All follow-up is defined from the day of completed radiotherapy (arm A: D1, arm B: D5 or D6-10 if modifications, see Section 6.5)

b If a second fraction is offered (see [Section 4.3.1](#)), evaluation must be scheduled 4 weeks +/- 4 days after the second fraction is delivered,. For all other patients, evaluations must be scheduled 8 weeks +/- 4 days from baseline

c Within 72 hours before randomization

d Only if baseline NRS score of target symptom is available

e Including pain medication, tranexamic acid, anticoagulants, laxatives, antidiarrheal medication, antiemetics and steroids

f Radiotherapy treatment within the same planning target volume (PTV) (additional fraction after 4 weeks in arm A is not considered reirradiation)

g I.e. hospital submissions and coding record related to radiotherapy

h All AE ≥grade 3/SAE

i Only AE ≥grade 3/SAE with suspected causality with radiotherapy

j To be performed within 4 days after decision

k Only if second fraction is offered. See [Section 4.3.1](#)

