#### **8.2.1.2. EORTC QLQ-C15 PAL**

The European Organization for Research and Treatment of Cancer Quality of Life Questionnaire- Core15-PAL.

Assessed at baseline and after 4, 8, 12 and 26 weeks of follow-up

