### **8.2.3. Health economics**

The 5 Level-EuroQol-5 Dimension (EQ-5D-5L) assessed at baseline and after 4, 8, 12 and 26 weeks of follow-up.

Costs related to attendance at the radiotherapy unit, transportation and hospitalization (including coding)

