### **8.3.2. Physician-assessed toxicity CTCAE**

Common Terminology Criteria for Adverse Events version 5.0.

Assessed baseline and after 4 weeks, 12 weeks and 52 weeks of follow-up.

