### **9.2. Statistical Hypotheses**

The primary hypothesis is that a radiotherapy schedule of 1-2 fractions of 8 Gy provides non-inferior patient-reported symptomatic relief as a schedule of five fractions of 5, assessed 12 weeks after completed radiotherapy (see [Section 9.1](#) for definition of the non-inferiority margin). The lower bound of the 95% confidence interval of the difference in mean symptom intensity of arm A is therefore hypothesized to be above the non-inferiority margin of -1.

If non-inferiority regarding symptom relief, and comparable QoL, toxicities and OS can be proved 12 weeks after the intervention a short-course schedule with 1-2 fractions will be recommend as standard of care. If non-inferiority can be proven only 4 weeks after the intervention, a single fraction schedule will be recommend for patients with a very short life expectancy where palliative radiotherapy is considered reasonable.

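### Baseline QLQ-C15 PAL and EQ-5D-5L may be completed after the patient knows the arm, because the baseline window ends at the start of radiotherapy, not at randomisation

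*Protocol*

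**What the plan says.** Section 4.1 sets the window: "Study-specific baseline evaluation will be performed between date of signed informed consent and intervention start". The same section has eligible patients "randomized to either arm A or arm B with an allocation ratio of 1:1 after collection of a signed informed consent", so allocation can happen anywhere between consent and the first fraction.

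The Schedule of Activities (Section 1.2) places randomisation, QLQ-C15 PAL, EQ-5D-5L and baseline CTCAE together in the Preparation column and gives them no order. NRS scores for the target symptom and for other symptoms stand in the earlier Screening column. Footnote d, attached to randomisation, reads "Only if baseline NRS score of target symptom is available". The only other footnote timed against randomisation is footnote c on the pregnancy test ("Within 72 hours before randomization"), which concerns eligibility and not outcome.

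The sections on the instruments add no order. QLQ-C15 PAL is "Assessed at baseline and after 4, 8, 12 and 26 weeks of follow-up", EQ-5D-5L is "assessed at baseline and after 4, 8, 12 and 26 weeks of follow-up", and CTCAE is "Assessed baseline and after 4 weeks, 12 weeks and 52 weeks of follow-up".

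Section 3 defines both QoL endpoints as change from baseline, under the exploratory objectives. Section 9.2 nevertheless opens its recommendation rule with "If non-inferiority regarding symptom relief, and comparable QoL, toxicities and OS can be proved 12 weeks after the intervention". The trial has no masking (title page, Section 6.3).

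**The concern.** A baseline serves as a reference only if the treatment arm cannot have influenced it. The arms differ in a way patients notice at once: one initial treatment visit against five. A patient who is relieved or disappointed by the allocation may answer a QoL form differently that day. If the reaction differs between arms, the baseline differs between arms for a reason unrelated to health. A change score then carries that difference into every follow-up comparison, at 4, 8, 12 and 26 weeks.

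Late completion is a practical possibility. Section 5 expects consent often to be collected at the attendance for radiotherapy planning, so consent, randomisation, planning CT and questionnaires may cluster around one visit in whatever order suits the site. Central randomisation, the bias measure named in Section 6.3, protects the allocation but not what is reported after it.

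At stake are the QoL comparison that Section 9.2 uses at 12 weeks as one condition for recommending the short course, and the EQ-5D-5L input to the health-economic comparison. The error could create a difference that does not exist or hide one that does.

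**Working it through.** **Step 1. What must precede randomisation?**

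| Item | Column in the Schedule | Required before randomisation? |
|---|---|---|
| Target-symptom NRS | Screening | Yes, footnote d |
| Other-symptom NRS | Screening | Scheduled earlier; not named in footnote d |
| Pregnancy test | Preparation | Yes, footnote c (eligibility) |
| QLQ-C15 PAL | Preparation | Not stated |
| EQ-5D-5L | Preparation | Not stated |
| Baseline CTCAE | Preparation | Not stated |

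Section 8 requires screening evaluations to be completed to confirm eligibility. The last three items are not eligibility criteria in Sections 5.1 and 5.2, so that rule does not reach them. The Section 4.1 window, which ends at the start of radiotherapy, is all that governs them.

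**Step 2. Which analyses use these baselines?** QoL and EQ-5D-5L are analysed as change from baseline (Section 3). Bladder and bowel toxicity is assessed at 4, 12 and 52 weeks, and Section 9.5.3 lists counts of events and of patients by grade. No CTCAE change score is defined. The primary endpoint is a change score, but its baseline is protected by footnote d.

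**Step 3. How would a shifted baseline act?** The documents give no figure for it, so the following is illustration on assumed values.

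The number per arm comes from Section 9.3. With margin 1, SD 2, one-sided 2.5% and 85% power, the standardised difference is 1/2 = 0.5. The two-sample t-test needs 72.8, so 73 per arm and 146 in total, with power 0.851. The plan's figure reproduces. For 25% loss, 146/0.75 = 194.7, so 195, against the stated 200. Nothing in this point changes the sample size.

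Let b be the arm difference in mean baseline report caused by knowing the arm, in SD units. If only a share of patients completes the forms late, the same share in each arm, then b = share × shift among them. Let rho be the correlation between baseline and 12-week score, with equal SDs and no true difference.

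- Change score: bias b, SE = √(2(1−rho)) × √(2/73).
- Baseline-adjusted: bias rho × b, SE = √(1−rho²) × √(2/73).
- Follow-up score alone: bias from this source 0.
- False-difference rate of a two-sided 5% test: Φ(bias/SE − 1.96) + Φ(−bias/SE − 1.96).

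For b = 0.2 and rho = 0.5, with √(2/73) = 0.1655:

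- Change score: SE = 1 × 0.1655; 0.2/0.1655 = 1.208; rate = Φ(−0.752) + Φ(−3.168) = 0.227.
- Adjusted: SE = 0.866 × 0.1655 = 0.1433; 0.1/0.1433 = 0.698; rate = Φ(−1.262) + Φ(−2.658) = 0.107.

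| b (SD) | rho | Change score | Baseline-adjusted |
|---|---|---|---|
| 0.1 | 0.3 | 8.0% | 5.4% |
| 0.1 | 0.5 | 9.3% | 6.4% |
| 0.1 | 0.7 | 12.2% | 9.1% |
| 0.2 | 0.3 | 17.5% | 6.7% |
| 0.2 | 0.5 | 22.7% | 10.7% |
| 0.2 | 0.7 | 34.5% | 22.0% |
| 0.3 | 0.3 | 33.4% | 8.8% |
| 0.3 | 0.5 | 44.1% | 18.2% |
| 0.3 | 0.7 | 64.8% | 42.7% |

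The table shows the mechanism and what adjustment can do. It does not estimate what will happen in this trial.

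**The case against.** The strongest reply is that little depends on this. The one baseline that carries the non-inferiority conclusion is collected before randomisation. QoL and EQ-5D-5L are exploratory, and Section 9.5.4 treats such analyses as hypothesis-generating. The recommendation rule in Section 9.2 concerns 12 weeks only and sets no margin for comparable QoL. The analysis model for QoL is largely left to an SAP that is not shown, and adjustment there would shrink the bias. Every follow-up questionnaire is in any case answered with the arm known. All of this stands, and it limits the weight of the point. It does not close the gap: the timing of data collection is fixed by the protocol, and no analysis plan can change when a form was completed.

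Some stronger readings are tempting but not supported.

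- A reader might infer that the primary result is at risk. Footnote d rules that out for this mechanism.
- A reader might infer that change from baseline is equally biased for CTCAE. No such change score is defined. What remains is that existing symptoms may be graded with the arm known.
- A reader might infer that the protocol directs sites to collect the forms late. It is silent on order. Sharing a column with randomisation proves nothing by itself, since the eligibility check and pregnancy test stand there too.
- A reader might infer that the damage could never be undone. Baseline adjustment reduces the bias from b to rho × b, and comparing follow-up scores alone avoids it, at the price of not using the baseline.
- A reader might want a bias in scale points. Neither the share of late baselines nor the size or direction of any shift is in the documents.

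Figure 1, the study timeline, is not reproduced in the text at hand and may show an order that the written text does not state.

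**Conclusion.** The point holds in a limited form. As written, the protocol permits the baseline QLQ-C15 PAL and EQ-5D-5L to be completed after allocation is known. This can bias their exploratory change-from-baseline comparisons, including the 12-week QoL condition in the recommendation rule. For baseline CTCAE the concern is smaller and of a different kind. The primary endpoint and the sample size are untouched.

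The size of the bias is unknown. On assumed shifts of 0.1 to 0.3 SD and correlations of 0.3 to 0.7, with 73 per arm, the false-difference rate runs from 8% to 65% on change scores and from 5% to 43% with baseline adjustment. If every site collects the forms before randomising, this bias is zero. The case for change rests less on size than on the fact that the bias is avoidable and that the protocol already applies the safeguard to its primary measure.

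**What to change.** In Section 4.1, end the window for the baseline questionnaires and the baseline CTCAE grading at randomisation instead of at the start of intervention. In Section 1.2, extend footnote d so that randomisation requires QLQ-C15 PAL, EQ-5D-5L and baseline CTCAE as well as the target-symptom NRS, and enforce this with an eCRF check before allocation is released.

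The cost is two wording changes and one eCRF check. Randomisation waits until two short questionnaires and one grading form are complete. No visit, assessment or patient is added.

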**Figure 1: Study timeline**

## 4.2. Scientific Rationale for Study Design

The principal research question is whether a short-course radiotherapy schedule of 1-2 fractions provide non-inferior patient-reported symptom relief compared to a schedule of 5 fractions, assessed 12 weeks after completed radiotherapy. If non-inferiority is established, and general QoL, toxicities and overall survival are comparable between the two study arms, a short-course schedule will be preferred, as it will be less burdensome for patients and provide improved exploitation of health care resources. A superiority study would therefore not be necessary in order to implement treatment results. Although superiority studies that fail to reject the null hypothesis are frequently interpreted as showing no differences between groups, they should be interpreted as indeterminate (77).

If non-inferiority can be proved only 4 weeks after completed radiotherapy, a single fraction schedule will be recommend for patients with a very short life expectancy for whom palliative radiotherapy is considered reasonable.

### 4.2.1. Participant Input into Design

A user representative is included in the study group, and has contributed to the preparation of the informed consent form, study questionnaires and study protocol. The user representative will be invited to the overall study group meetings.

## 4.3. Justification for Radiotherapy Dose

### 4.3.1. Second Radiotherapy Fraction in Arm A

For patients in arm A receiving an initial single fraction of radiotherapy, a second fraction *may* be offered at the 4-week follow up visit (attendance or telephone) if the clinical oncologist and the patient find it appropriate, and if at least one of the following occurs:

- Unsatisfactory symptom relief, defined as  $\leq 2$  point improvement on the NRS scale compared to baseline
- Initial symptomatic effect, but rapid deterioration of symptoms

If systemic treatment is resumed after the first fraction ([Section 5.1](#) and [6.8](#)), and the patient is scheduled for a second fraction after the 4- week follow-up visit, systemic treatment must be paused from the second fraction is determined until one week after completed radiotherapy.

Patients in both study arms may not be included in other interventional clinical trials until the 4 week assessment is completed ([Section 6.8](#)).

#### **4.4. End of Study Definition**

The end of study is defined as the last patient last visit (LPLV), i.e. the data when the last patient complete the study. A patient is considered to have completed the study if he/she has completed all phases of the study including the last visit at 52 weeks.

The study may be terminated by the investigators, trial steering committee and/or sponsor for clinical or administrative reasons.

The end of study will be reported to the Regulatory Authority and institutional review boards (IRB)/independent ethics committee (IEC) within 90 days, or 15 days if the study is terminated prematurely. The investigators will inform included patients of the premature end of study and ensure that appropriate follow-up is arranged for all patients involved

## 5. Study Population

Patients will be recruited from their local oncology department or palliative unit, and must be considered as candidates for palliative radiotherapy according to the two study arms by their treating physician. To minimize the total burden on the patient, the recruitment procedure is customized to standard clinical practice in order to limit additional attendances at the hospital.

If all inclusion and exclusion criteria are met, patients will be informed about the study by their treating physician or nurses, and asked to participate. A written informed consent form will be handed out. If the patient is interested in participation, the patient will be contacted by a study nurse after sufficient time to consider participation. This contact may be in connection with a planned attendance at the hospital, or by telephone. Sufficient time to consider participation include time to read, understand and reflect upon the written informed consent form, as well as to have time to consult next of kin or primary physician regarding potential participation. If the patient is contacted by telephone, information about the specific telephone number and the date and time of the telephone call will have been provided in advance. There will be allocated enough time in order to answer all potential questions the patient might have. If the patient wants to participate, the signed informed consent will be collected in connection with a planned attendance at the hospital. This attendance will be scheduled by the study nurse, and may often be in connection with the standard radiotherapy planning procedures.

To ensure inclusion of all eligible patients, participants may also be identified by study personnel allocated to the radiotherapy unit, after referral to radiotherapy by the treating physician. Study personnel at the radiotherapy unit will be indicated on the study delegation log, but will not have a dedicated treatment responsibility towards the patient. If possible participants are identified, study eligibility will be discussed with the treating physician and PI. If considered eligible for inclusion, patients will receive the written informed consent form by post or Helse Norge in advance, and will subsequently be informed about the study at the planned attendance scheduled for radiotherapy planning procedures. If a possible participant is identified the same day as this planned attendance, study personnel or the treating physician will first inform about the study in connection with the attendance, and the written informed consent form will subsequently be handed out. If the patient is interested in participation, further procedures will be in accordance with the description in the section above.

### 5.1. Inclusion Criteria

- Histologically verified primary cancer originated from gastrointestinal, urological or gynecological organs (histological verification can be performed on other lesions than the symptomatic pelvic tumor)

- Patients unsuitable for curative treatment due to either advanced disease or medical contradictions (i.e. comorbidity, old age or poor general condition)
- Primary, residual, recurrent or metastatic pelvic tumor from the abovementioned cancers not amenable for curative treatment
- Tumor-related symptoms within the following five predefined categories: pain, bleeding, bowel dysfunction, lower urinary tract dysfunction and vaginal dysfunction
- Considered as a candidate for palliative radiotherapy according to both study arms
- Patient reported average severity of symptoms  $\geq 4$  on a NRS scale of 0-10
- $\geq 18$  years of age
- Speaks and understands Norwegian or English
- Ability to understand and willing to sign a written informed consent form
- ECOG performance status of 0-3
- Expected survival  $> 12$  weeks
- Able to pause systemic cancer treatment for one week prior to, during, and one week after radiotherapy
- Women of childbearing potential (WOCBP) should have a negative highly sensitive serum pregnancy test within 72 hours prior to randomization. WOCBP must agree to the use of highly effective birth control methods or abstain from heterosexual sexual activity from randomization until completed study intervention

